### Two-month repeat QFT-plus

For any malnourished or parasite positive participant with a negative or indeterminate QFT-Plus result during screening, a follow up visit is conducted approximately 2 months later for repeat QFT-Plus. Any HHC positive upon repeat testing is enrolled for longitudinal follow up. For those who are malnourished, still QFT-Plus negative upon repeat testing, but have a HHC already enrolled into the intervention due to malnutrition, the participant is enrolled into the study for longitudinal follow up.

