**Methods:**

This is a 5-year prospective clinical trial at Jawaharlal Institute of Post Graduate Medical Education and Research in Puducherry, Tamil Nadu, India. We aim to enroll 760 household contacts (HHC) of adults with active TB in order to identify 120 who are followed prospectively for 2 years: Thirty QuantiFERON-TB Gold Plus (QFT-Plus) positive HHCs ≥ 18 years of age in four proposed groups: (1) undernourished (body mass index [BMI] < 18.5 kg/m^2^); (2) participants with a BMI ≥ 18.5 kg/m^2^ who have a parasitic infection (3) undernourished participants with a parasitic infection and (4) controls—participants with BMI ≥ 18.5 kg/m^2^ and without parasitic infection. We assess immune response at baseline and after food supplementation (for participants with BMI < 18.5 kg/m^2^) and parasite treatment (for participants with parasites). Detailed nutritional assessments, anthropometry, and parasite testing through polymerase chain reaction (PCR) and microscopy are performed. In addition, at serial time points, these samples will be further analyzed using flow cytometry and whole blood transcriptomics to elucidate the immune mechanisms involved in disease progression.

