### Parasitology

Participants are provided with stool containers for at home stool collection during screening and follow up visits (months 1, 3, 6, and 12). Stool samples are collected in three containers containing (1) 10% formalin (for diagnostic microscopy); (2) Zn-PVA (for polymerase chain reaction [PCR] testing); and (3) RNAlater (for microbiome testing on a subset of participants). If there is a shortage of Zn-PVA, stool samples are split into two with half the sample being stored in 5–10% formalin and the other half unpreserved. QuantiFERON-TB Gold Plus (QFT-Plus) negative screened participants only have stool collected for microscopy. PCR is conducted to confirm infections with *Ancylostoma duodenale, Necator americanus, Ascaris lumbricoides, Strongyloides stercoralis*, and *Trichuris trichiura*. We define parasite infection as having one or more helminth infections. Those with helminth infections are referred to their PHC for treatment. Month 1 microscopy and PCR is conducted on QFT-Plus positive parasite study arm participants to confirm that parasite infections have resolved. The parasitology technician conducts stool concentration, sedimentation, and trichrome staining for parasite identification. All parasite positive samples and diagnostic queries undergo confirmation by the head of the parasitology department. The parasitology technician completes a quarterly external quality assurance (EQA) program (Wisconsin State Laboratory of Hygiene) [38]. All remaining samples are stored in – 80 C freezer.

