### Nutritional intervention

Undernourished participants are re-consented and enrolled into the study intervention (food and micronutrient supplementation) for 6 months followed by an additional 18-months of extended follow-up. In order to encourage adequate nutritional intake, even in the context of food sharing, the nutrition intervention food rations provided are sufficient to feed all household members. At enrollment, participants are asked the number and age of household members.

The kcal requirements for the food supplements were derived from the Indian TB Nutrition Guidelines that men and women require 2500 and 2100 kilocalories (kcal) respectively; thus, HHCs receive 2600 kcal each with children 13 years and younger receiving 1300 kcal [39]. The 2600 kcal/day needs were determined based off clinical feeding guidelines of 35–40 kcal/kg for undernourished patients [40] to achieve a BMI level considered optimal (21 kg/m^2^) based on the National Institute of Nutrition (NIN) in India’s recommendation for optimizing health and nutrition. In order to determine the contents of the food ration, we consulted local partners, TB experts in India, and nutritionists to create a meal package that is locally acceptable, suitable for vegan and omnivores, and that gives participants dietary variety without compromising nutritional quality. The meal package is comprised of pulses, white rice, groundnuts, and oil; nutrition calculations were made from standard nutrient analysis based on the *Exchange Lists for Meal Planning*, by the Academy of Nutrition & Dietetics in conjunction with the American Diabetes Association [41] (Table 1). These foods were also selected because they can be easily transported to the participant homes and they do not require refrigeration. Enrolled participants also receive a multiple micronutrient supplement (Life-Extension Two-Per-Day Tablets) [42] which contains over 100% of the RDA for Vitamins A, B6, B12, C, D3, and E.

**Table 1 Tab1:** Tuberculosis: Learning the Impact of Nutrition (TB LION) nutritional intervention package for one adult per day

Food category	Food item	Kilocalories	Protein (g)	Fat (g)
Fat (5 g/day)	Vegetable oil	45	0	5
Pulse (117 g/day)	Red gram, green gram, and black gram	468	23.4	1.5
Grains (325 g/day)	White rice	1301	22.75	2.3
Nuts (143 g/day)	Ground nuts	786	35.75	70.1
Total		2600	81.9	78.8

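### Contacts who enter through the two-month QFT-Plus retest may already have been dewormed or fed, so their enrolment sample may not be an untreated baseline

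*Protocol article*

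**What the plan says.** All references are to the Protocol article.

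- **Retest and entry** (Two-month repeat QFT-plus). The rule applies "For any malnourished or parasite positive participant with a negative or indeterminate QFT-Plus result during screening"; for these people "a follow up visit is conducted approximately 2 months later for repeat QFT-Plus". After that, "Any HHC positive upon repeat testing is enrolled for longitudinal follow up". The same section also enrols malnourished contacts who remain QFT-Plus negative, provided a housemate is already in the intervention because of malnutrition.
- **Parasite treatment** (Parasitology). "Those with helminth infections are referred to their PHC for treatment". The sentence does not depend on QFT-Plus status and is not tied to enrolment or baseline sampling. At screening, QFT-Plus "negative screened participants only have stool collected for microscopy". Clearance is checked in people already in the arms: "Month 1 microscopy and PCR is conducted on QFT-Plus positive parasite study arm participants to confirm that parasite infections have resolved".
- **Feeding** (Nutritional intervention). For an enrolled undernourished participant, "the nutrition intervention food rations provided are sufficient to feed all household members", for 6 months. The micronutrient tablets go to enrolled participants.
- **Analysis** (abstract, Methods; Statistical analyses). "We assess immune response at baseline and after food supplementation" and, in those infected, after parasite treatment. Treatment effects are analysed by mixed models on repeated measurements within a person. Follow-up visits are counted from enrolment (Longitudinal follow-up).

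**The concern.** Aims 1 and 2 compare undernourished and parasite-infected contacts with contacts who have neither condition. That needs samples taken while the condition is present and untreated. Aims 3 and 4 estimate change after feeding and after parasite treatment, which needs a sample from before each. The retest pathway leaves a gap of about 2 months in which either treatment can begin, and the entry rule does not look at that gap.

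A person already cleared of helminths at enrolment has little or no deworming response left to show. If counted as parasite-infected, that person makes the parasite arm look more like the uninfected arms. If counted as uninfected, a recently treated person enters the comparator. A contact already eating a housemate's ration starts the nutrition analysis part-way through feeding. With 30 people per arm, a few such entrants can matter.

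**Working it through.** No stated sample size, power or error rate is at issue. The only related figure agrees with itself: 4 arms × 30 = 120. The check is whether the stated rules, followed in order, allow treatment before baseline.

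**Deworming route**

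1. At screening, a contact has helminths on microscopy and a negative or indeterminate QFT-Plus.
2. The contact is referred for treatment. Nothing holds the referral until the retest.
3. The article checks clearance at month 1 in arm participants, so it expects infection to have resolved on that time scale, which is shorter than the retest gap.
4. About 2 months after screening, QFT-Plus is repeated; if positive, the contact is enrolled. The retest section names no repeat stool test and no check of treatment received.
5. The enrolment sample may therefore follow treatment. The screening sample does not simply replace it: someone who went from negative to positive was QFT-Plus negative at screening, while the arms are defined for QFT-Plus positive contacts.

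**Food route**

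1. An undernourished contact is QFT-Plus negative or indeterminate at screening, and an undernourished housemate is already on rations.
2. The household ration covers the contact during the wait. The tablets do not.
3. The contact is enrolled if positive at retest. If malnourished and still negative, the contact is enrolled precisely because such a housemate exists.
4. The wait is at most about 2 months, against a 6-month intervention: 2/6 = one third.

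An undernourished contact with no such housemate is not affected by this route.

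**Illustrative size (inputs assumed, not in the article)**

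Dilution of the parasite contrast = (share of parasite-arm places filled by retest entrants) × (share of those cleared before enrolment).

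- Low: 0.05 × 0.80 = 0.04, or 4% (3 of 60 parasite-arm places are retest entrants).
- High: 0.20 × 1.00 = 0.20, or 20% (12 of 60).

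This treats clearance as removing the whole immune effect at once, so it is an upper bound for the chosen inputs.

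For the consequence, take a paired change in one arm of n = 30, two-sided α = 0.05, and suppose 80% power without dilution. The standardised change is then dz = (1.960 + 0.842)/√30 = 0.51. If a share f has no response left to show:

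- Entrants kept in: power = Φ(dz × (1 − f) × √30 − 1.96)
- Entrants left out: power = Φ(dz × √(30 × (1 − f)) − 1.96)
- n per arm to restore 80% if kept in: 30/(1 − f)², rounded up

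| f (assumed) | Power, kept in | Power, left out | n to restore 80% if kept in |
|---|---|---|---|
| 0 | 80% | 80% | 30 |
| 10% | 71% | 76% | 38 |
| 20% | 61% | 71% | 47 |
| 30% | 50% | 65% | 62 |

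On these assumptions, leaving pre-treated entrants out costs less power than keeping them in.

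**The case against.** **Material not shown.** The specimen schedule (Additional file 1, Table S1) and the study schematic (Fig. 1) are not visible. Cells and RNA may be collected at screening, and stool may be repeated when a retest entrant is enrolled. The article says that PCR confirms infection, and a QFT-Plus negative contact has no PCR stool from screening, so a new stool at enrolment may be implied. This stands. A reader might infer that cleared people are placed in parasite arms on the strength of the screening stool; no passage says so.

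**Screening samples may serve for some.** An indeterminate result is not a negative one, and the article itself describes weakened Th1 responses in undernutrition and parasitic infection, so a negative test might reflect a blunted response. This stands in part. A reader might infer that every retest entrant lacks an untreated baseline; the documents support only that some may.

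**Size and direction.** Uptake and timing of treatment are not stated. Contacts are first evaluated 8 weeks after the index case is enrolled, so later converters may be few. The Discussion treats the time course of immune recovery as an open question. QFT-Plus status also changed in converters, which could move immune readouts either way. This stands. A reader might take 4% to 20% as an estimate, or bias towards no effect as established; neither is supported.

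**Partial records exist.** Diet is recalled at screening and household food is weighed every two weeks. Ration exposure is thus partly recorded at household level, but the article does not link it to a retest entrant's baseline.

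**Analysis exclusions belong in the SAP.** That may be so for the detail. But the unconditional entry rule and the before/after design are both stated in the article, and they conflict as written. Exposure not recorded at enrolment may be hard to reconstruct later.

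**Conclusion.** The point holds as a design conflict of unknown size. The retest rule, the referral rule and the household ration, taken as written, allow people already dewormed or already sharing rations to enter the baseline comparisons and the before/after models. The deworming route can touch any parasite-positive retest entrant. The food route is narrower, but it includes the still QFT-Plus negative contacts whom the article enrols.

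The power figures show only that arms of 30 have little slack; they rest on an assumed 80% starting power and an assumed f, and they ignore any change in variance.

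**What to change.** Leave treatment referral and household feeding as they are, and reconcile the timing of both relative to baseline sampling across the sections Parasitology, Two-month repeat QFT-plus and Nutritional intervention. For anyone enrolled after the retest:

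1. State which visit and which sample is the baseline. Establish parasite status at that enrolment with the same microscopy and PCR used for other arm participants.
2. Record any deworming and any household ration received since screening.
3. Flag these entrants in the data.
   - Leave those dewormed since screening out of every baseline arm contrast and out of the Aim 4 before/after analysis. This includes not counting them as uninfected in the U or W arm, which reassignment on a new stool result alone would allow.
   - Leave those already on a household ration out of the baseline nutrition contrast and the Aim 3 before/after analysis.
   - Add a sensitivity analysis that includes them, and keep all of them for TB follow-up.

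The cost is a short statement on baseline and arm assignment, two form fields, and one stool sample with tests the study already runs. The downside is that a few retest entrants no longer count towards an arm's 30 in the affected analyses.

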### Nutritional intervention

Undernourished participants are re-consented and enrolled into the study intervention (food and micronutrient supplementation) for 6 months followed by an additional 18-months of extended follow-up. In order to encourage adequate nutritional intake, even in the context of food sharing, the nutrition intervention food rations provided are sufficient to feed all household members. At enrollment, participants are asked the number and age of household members.

The kcal requirements for the food supplements were derived from the Indian TB Nutrition Guidelines that men and women require 2500 and 2100 kilocalories (kcal) respectively; thus, HHCs receive 2600 kcal each with children 13 years and younger receiving 1300 kcal [39]. The 2600 kcal/day needs were determined based off clinical feeding guidelines of 35–40 kcal/kg for undernourished patients [40] to achieve a BMI level considered optimal (21 kg/m^2^) based on the National Institute of Nutrition (NIN) in India’s recommendation for optimizing health and nutrition. In order to determine the contents of the food ration, we consulted local partners, TB experts in India, and nutritionists to create a meal package that is locally acceptable, suitable for vegan and omnivores, and that gives participants dietary variety without compromising nutritional quality. The meal package is comprised of pulses, white rice, groundnuts, and oil; nutrition calculations were made from standard nutrient analysis based on the *Exchange Lists for Meal Planning*, by the Academy of Nutrition & Dietetics in conjunction with the American Diabetes Association [41] (Table 1). These foods were also selected because they can be easily transported to the participant homes and they do not require refrigeration. Enrolled participants also receive a multiple micronutrient supplement (Life-Extension Two-Per-Day Tablets) [42] which contains over 100% of the RDA for Vitamins A, B6, B12, C, D3, and E.

**Table 1 Tab1:** Tuberculosis: Learning the Impact of Nutrition (TB LION) nutritional intervention package for one adult per day

Food category	Food item	Kilocalories	Protein (g)	Fat (g)
Fat (5 g/day)	Vegetable oil	45	0	5
Pulse (117 g/day)	Red gram, green gram, and black gram	468	23.4	1.5
Grains (325 g/day)	White rice	1301	22.75	2.3
Nuts (143 g/day)	Ground nuts	786	35.75	70.1
Total		2600	81.9	78.8

The field team visits households every other week to replenish the food, assess food consumption and changes in participant health. During the initial food delivery visit, nutritionists provide study food containers and then weigh each container, taring the scale to accurately account for the weight of container. They then add the calculated amount of each food item and mark each container with a black marker to indicate the fill line. The weight of each respective food container is recorded. Nutritionists return to the household every 2 weeks to evaluate the remaining food and vitamin supplement. The remaining food (for each item) is poured into a tared tray, weighed and recorded. Using the initial calculated food quantity and remaining quantity, nutritionists calculate the amount of food consumed by the household and the amount required to replenish the stock which is added to the container before the remaining food to minimize food expiry.

Severely undernourished participants (BMI 14–16) receive partial supplementation for the first 2 weeks of intervention; 30% for the first week and 50% the second week. By the third week, participants will receive 100% of the supplementation. Study staff assess electrolytes (potassium, magnesium, and phosphorus) and conduct an assessment for food consumption and changes in participant health before replenishing the week’s food supply. If electrolyte results are normal, food supply is increased; however, if food is not being consumed based on observation, a second week of the partial ration is provided and electrolytes re-checked. If electrolyte results are abnormal, food supplementation is stopped, and the participant is referred to the hospital. HHC bi-weekly visits detailed above will begin once 100% of the ration is received.

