### Study population

Study staff identify new TB index cases (ICs) through the National Tuberculosis Elimination Programme (NTEP). Inclusion criteria are: (1) Age ≥ 18 years; (2) New sputum-smear positive (≥ 1+ acid fast bacilli [AFB]) pulmonary TB that is culture or GeneXpert positive; (3) No history of TB treatment; (4) Have at least one household contact (HHC) with whom they shared a house during the previous month; (5) Agree to have HHCs contacted. Exclusion criteria include: (1) Pregnant; (2) No GeneXpert or culture confirmation and unable to provide sputum sample; (3) No HHCs; (4) Known MDR or XDR TB; (5) BMI < 14 kg/m^2^ as to avoid refeeding complications; (6) Kwashiorkor, lower extremity edema or lower extremity neuropathy in those with BMI < 14.

Inclusion criteria for HHC include: (1) Age 18–60 years; (2) Housemate of an eligible TB case for at least the past month; (3) HIV seronegative or willing to be tested; (4) Willing to be tested for pregnancy. Exclusion criteria include: (1) Pregnant at enrollment; (2) Having known diabetes mellitus or evidence by hemoglobin A1C (HbA1c) > 6.5%; (3) GeneXpert positive among those able to produce sputum; (4) History of TB disease; (5) Karnofsky score ≤ 10 (moribund); (6) If BMI < 16 kg/m^2^, abnormal potassium, magnesium, or phosphorus; (7) Kwashiorkor; pitting edema; neuropathy [23].

All HHCs in the home are approached for enrollment. All eligible household contacts in one house are enrolled for prospective follow up if the HHCs fall in overlapping study arms. If there are more than one eligible HHCs, but no overlapping study arm designations, any malnourished HHC screened is enrolled to limit selection bias. We expect to enroll 760 HHCs to identify 120 study participants for longitudinal follow-up. Sample size was determined by participant data from the Regional Prospective Observational Research for Tuberculosis (RePORT India) cohort study [24].

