## Discussion

The TB LION study allows us to assess an overlooked obstacle for TB elimination in India—undernutrition—and to evaluate the potential role for parasitic infections in the Indian context. There is a paucity of studies that have assessed the impact of undernutrition on the immune response during Mtb infection and more importantly whether these can be reversed with interventions. The TB LION study, with its ample macronutrient and micronutrient supplementation, rigorous monitoring of nutritional intake, and detailed immunologic analyses address these barriers.

One strength of the study is that we address how the impact of undernutrition is modulated by parasitic infections that are common in India. Intestinal parasites can decrease absorption of key macronutrients (e.g., protein) and micronutrients (e.g., zinc) [21]. Parasites may also have a direct effect on risk of TB progression by inducing Th2 responses and weakening Th-1 (and Th17) responses needed to control Mtb [53]*.* Antihelminth treatment in persons with Mtb infection and Schistosoma or Strongyloides coinfection is associated with increased CD4^+^ IFNγ^+^  cells, suggesting improvement in immune response [54], but data are needed to address whether the implications are similar for other parasites. The TB LION study further informs the role of parasitic infection on risk of progression to TB disease, the time course of improvement in these responses after parasite treatment, and the durability of the response. Furthermore, we are able to address the interplay of undernutrition and parasite infections.

The TB LION study is an ambitious study, with potential to yield very meaningful information. We are confident that our design and methodology, with the addition of sample collection to address the impact of potential COVID-19 infection (through serology), provides comprehensive data to draw sound conclusions regarding the risk of progression to active TB among HHCs. Another key strength of this study is the prospective follow up with clinical assessment on all study participants. Extensive data collection on all participants allows for thorough comparative analyses within and across participant groups. We perform a qualitative assessment of the intervention, a cost-effectiveness analysis of nutritional interventions, and assessments of micronutrient contributions to immune response.

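### Some well-nourished participants (W, WP) may live in homes that receive the whole-household ration, yet would be analysed by arm label as unfed

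*Protocol article*

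**What the plan says.** The abstract assigns "food supplementation (for participants with BMI < 18.5 kg/m^2"), that is, to arms U and UP only. The Nutritional intervention section supplies the food by home: "the nutrition intervention food rations provided are sufficient to feed all household members", and "HHCs receive 2600 kcal each with children 13 years and younger receiving 1300 kcal". Undernourished participants are "enrolled into the study intervention (food and micronutrient supplementation) for 6 months followed by an additional 18-months of extended follow-up". The tablet is described separately: "Enrolled participants also receive a multiple micronutrient supplement"; nothing says that it goes to the rest of the home.

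Two passages govern who is followed from one home. Study population states: "All eligible household contacts in one house are enrolled for prospective follow up if the HHCs fall in overlapping study arms". Where arms do not overlap, it enrols the malnourished contact. It does not define *overlapping*. Two-month repeat QFT-plus retests malnourished or parasite-positive contacts whose first result was negative or indeterminate, and then: "Any HHC positive upon repeat testing is enrolled for longitudinal follow up". It mentions no check on who in the home is already in follow-up.

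Under Statistical analyses, the effects of feeding and of parasite treatment over time are estimated from repeated measurements on the same person in mixed models. The Discussion also promises comparisons between arms: "Extensive data collection on all participants allows for thorough comparative analyses within and across participant groups".

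**The concern.** The four arms cross two exposures. UP receives food and parasite treatment, U food, WP parasite treatment, and W neither. WP is thus the only arm that can show parasite treatment without food, and W is the only reference over time without either. Because food reaches everyone in the home, the arm label does not identify who had access to it. A WP participant in a ration home may eat study food in the same months in which the response to parasite treatment is measured, so that person's own change mixes the two. A W participant in such a home is not an unfed reference after baseline. The article has no rule for either case.

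**Working it through.** **Step 1: mixed homes at screening.** Four pairs would put a fed and an unfed arm in one home: U+W, U+WP, UP+W and UP+WP. If *overlapping* means the same arm, the rule in Study population admits none of them; only the malnourished contact enters. If it includes arms that share parasitic infection, UP+WP is admitted and the other three are still excluded. (A wider reading, in which being parasite-free also counts as shared, would admit U+W. I do not rely on it.)

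**Step 2: the retest.** This route stays open under either reading, because nothing says the same-home rule is applied again. It works in two directions:
- (a) A W or WP contact is in follow-up from screening. A malnourished housemate turns positive about 2 months later and enters U or UP, and the home begins to receive rations.
- (b) A U or UP contact is in follow-up and the home is already receiving rations. A well-nourished, parasite-positive housemate turns positive on retest and enters WP.

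W can be reached by (a) but not by (b), since the retest covers only malnourished or parasite-positive contacts. The further provision for malnourished contacts who stay negative adds people only in homes already in the intervention, so it opens no new route.

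**Step 3: timing.** The ration lasts 6 months, and visits fall at 2 weeks and months 1, 3, 6, 12, 18 and 24. I assume that the ration starts promptly when the malnourished contact is enrolled.
- UP and WP enrolled together: the ration covers months 0 to 6, so the WP visits from 2 weeks to month 6 are exposed.
- Route (a): the ration runs from about month 2 to month 2 + 6 = 8. Baseline, 2 weeks and month 1 are clean. Months 3 and 6 fall 3 − 2 = 1 and 6 − 2 = 4 months into the ration. Month 12 falls 12 − 8 = 4 months after it ends.
- Route (b): the WP participant enters with up to about 2 months of ration behind and about 6 − 2 = 4 months to come. Visits to month 3 are exposed. So is the baseline, if it is drawn at that enrolment.

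**Step 4: the plan's own figures.** 4 × 30 = 120 followed, as stated. Table 1 energy: 45 + 468 + 1301 + 786 = 2600 kcal, as stated. The article gives no significance level, power, effect size or standard deviation for a comparison between arms, so there is no power figure to reproduce. It gives no household composition from which the number of exposed W/WP participants could be derived.

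**Step 5: illustration of size, all inputs assumed.** Let f be the share of an unfed arm living in ration homes, and g their response to food as a fraction of the full food effect F. If effects add:
- Mean change in WP = (effect of parasite treatment) + f·g·F. With f = 10% (3 of 30) the added part is 0.10F at g = 1 and 0.05F at g = 0.5. With f = 30% (9 of 30) it is 0.30F and 0.15F.
- A fed-minus-unfed difference in change becomes δ(1 − f·g).

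Take 30 v 30, two-sided 5%, independent participants, and δ set to give 80% power without sharing: δ = (1.960 + 0.842) × √(2/30) = 0.723 SD. Then power = Φ[0.723(1 − f·g)/√(2/30) − 1.960]. For f = 10% and g = 1: 0.723 × 0.90 = 0.651, power 71%. Leaving the exposed people out gives 30 v 30(1 − f) with δ unchanged.

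| f | kept, g = 1 | kept, g = 0.5 | left out |
|---|---|---|---|
| 5% | 76% | 78% | 79% |
| 10% | 71% | 76% | 78% |
| 20% | 61% | 71% | 75% |
| 30% | 50% | 66% | 72% |
| 50% | 29% | 56% | 63% |

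**The case against.** The strongest reply is that the same-home rule already keeps out most mixed homes, and that what remains is narrow. Route (a) needs a malnourished contact who is negative or indeterminate at screening, about 8 weeks after the index case was enrolled, who then turns positive in a home where a W or WP contact is already followed. That stands: the share may well be small.

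A reader might infer that the W and WP arms as such receive the intervention and lose their value as comparators. The documents do not support that. Only co-housed individuals would be exposed, to the food and not, as stated, to the tablet, and for up to 6 months. Baseline comparisons precede feeding, apart from a possible late baseline in route (b).

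A reader might also infer that Aim 3 is diluted. That is not supported either. The feeding effect is modelled as change within U and UP participants, which a housemate's eating does not alter, and there is no undernourished unfed arm against which it was to be contrasted.

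It is also fair that covariates can be left to an analysis plan, and that 24-hour recalls (months 3, 6, 12 and 24) measure each participant's diet. But who may be enrolled and whom the ration reaches are protocol matters. Ration use is weighed per household, and the article states no analysis that uses the recalls to classify exposure. The within-person model does not protect Aim 4, because food and parasite treatment overlap in the same person.

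**Conclusion.** The point holds in a limited form. As written, the protocol allows some W and WP participants to be followed in ration homes: by the retest whatever *overlapping* means unless the same-home rule is applied again, and by UP+WP homes on one reading of the term. For those people, change after parasite treatment in WP (Aim 4) is mixed with food, and follow-up comparisons against W are not against unfed people. Aims 1 and 2 at baseline and the within-person feeding effect are largely intact.

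The size is unknown. The table rests on an assumed share, an assumed response and an assumed effect; full response in people with BMI of 18.5 or more is best taken as an upper bound. The loss is modest if the share is small and serious only if co-enrolment is common. The study is exploratory, so this does not undermine it, but it should be corrected because the correction is cheap.

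**What to change.** 1. In Study population, define *overlapping study arms*, and state that the same rule applies to anyone enrolled after the two-month retest, with regard to contacts from that home already in follow-up.
2. For every W and WP participant, derive from the delivery records whether the household receives study rations and from what date. For late-enrolled WP participants, record whether the baseline sample came before or after that date.
3. In the Aim 4 model, and in any follow-up comparison across arms, enter household ration as a time-varying exposure instead of relying on the arm label. Add a sensitivity analysis that leaves out W/WP samples taken after the ration starts.

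The cost is one derived variable from records already kept, a sentence or two in the enrolment rule and one in the analysis. The downside is somewhat fewer unfed W/WP person-visits: in the illustration, leaving out 10–30% of the comparator arm lowers power from 80% to 78–72%, against 71–50% if they are kept as unfed and respond fully, or 76–66% if they respond by half. Nothing in the food intervention itself needs to change.
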